### Outcome measures

The primary efficacy endpoint measure of the Poniy trial is the rate of surgical site infections within 30 days after the operation, according to CDC criteria, which constitute an internationally accepted standard definition [9] (Table 1). If the patient’s wound cannot be evaluated on postoperative day 30, a clinical evaluation according to the CDC criteria up to postoperative day 35 will be allowed.

The following outcome measures have been defined as secondary endpoint measures:Duration of hospital stay (in days);Rate of reoperation in both groups;Duration of postoperative antibiotic treatment in both groups within 30 days (in days);Duration of NPIT therapy (in days) in the interventional arm;Wound pain, as assessed by a visual analogue scale (graded from 1 to 10) in both groups;Rate of wound complications other than wound infections in both groups;Number of postoperative severe adverse events in both groups within 30 days.

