### Statistical methods

#### Sample size calculation

Sample size calculation is based on the primary endpoint measure (whether or not there is surgical site infection, according to CDC) within 30 days post operation [9] and was conducted by using nQuery Advisor® software version 7.0 (Statistical Solutions Ltd, Cork, Ireland). Based on the assumption that the percentage of patients developing postoperative wound infections in a surgical population undergoing open colorectal surgery is approximately 25 % for the control group (based on results from previous randomized controlled trials in abdominal surgery [14, 15, 17]) and can be reduced to 12.5 % in the experimental intervention arm, a group sample size of 152 patients would need to be compared using the chi-square test, to achieve 80 % power in detecting this difference in surgical site infection rate at a two-sided level of significance of 5 %. Under the assumption of a drop-out rate of up to 15 %, a total of 340 patients (170 per group) need to be enrolled in the study. Owing to the broad inclusion criteria and the limited number of exclusion criteria, the limited study time per patient (30 days), as well as the comprehensible nature of the trial, no more than 100 patients are expected to fail the screening process. Therefore, the total number of patients needed for screening is 440 (Fig. 1).

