#### Analysis populations

##### Intention-to-treat population

The intention-to-treat population contains all patients who have participated in visit 2 (surgery), independent of the intervention they receive (control or NPIT). Analysis will occur as randomized. Patients who unexpectedly receive a laparoscopic or laparoscopic assisted operation (exclusion criterion) will be excluded from the intention-to-treat population. Missing primary endpoint data in the intention-to-treat population will be treated as follows: data missing because of death or relaparotomy will be counted as surgical site infection in both groups. Data missing for other reasons (e.g., lost to follow-up) will not be counted as surgical site infection in either group.

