##### Per-protocol population

The per-protocol population contains all patients included in the intention-to-treat population as treated (not as randomized). The following patients will be excluded: (a) patients who receive a surgical wound dressing that is not predefined in the randomization scheme (i.e., neither an NPIT system nor a standard sterile dressing); (b) patients who do not reach visit 6 for reasons other than death or relaparotomy. Patients who die or undergo relaparotomy will be counted as having surgical site infections in both groups.

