#### Sensitivity analysis of the primary endpoint measure

The primary endpoint analysis will be repeated in the per-protocol and surgical site infection population. Further sensitivity analyses will be performed as follows: (a) in the surgical site infection population, all missing data will be imputed as surgical site infections in both groups; (b) in the surgical site infection population, all missing data will be imputed as non-surgical site infection in both groups; (c) in the surgical site infection population, missing data will be imputed as surgical site infections in the intervention group, but as non-surgical site infection in the control group; (d) a time-to-event analysis will be performed in the surgical site infection population according to Kaplan–Meier analysis.

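### As worded, the per-protocol analysis counts every death or relaparotomy as infection, while the primary analysis does so only when the endpoint is missing; the wording must settle one rule

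*Protocol article*

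**What the plan says.** The primary endpoint (Outcome measures) is "the rate of surgical site infections within 30 days after the operation, according to CDC criteria".

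Three statements under Statistical methods bear on how a death or relaparotomy enters that endpoint:

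- Intention-to-treat population, used for the primary analysis. Within its rule for missing primary endpoint data: "data missing because of death or relaparotomy will be counted as surgical site infection in both groups". Data missing for any other reason count as no infection.
- Per-protocol population. After two exclusions, the second of which removes patients who miss visit 6 for any cause except death or relaparotomy: "Patients who die or undergo relaparotomy will be counted as having surgical site infections in both groups". Nothing here refers to missing data.
- Sensitivity analysis of the primary endpoint measure: "The primary endpoint analysis will be repeated in the per-protocol and surgical site infection population".

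**The concern.** A relaparotomy does not in itself make the endpoint missing. Table 2 schedules documentation of reoperation at visits 3 to 6, alongside the blinded infection assessment. Reoperation is a secondary endpoint, and only a planned relaparotomy is an exclusion criterion. Table 1 treats reoperation as an occasion on which infection may be found, not as an infection. The protocol therefore allows for patients who are reoperated on, stay in follow-up and have an observed CDC status of no infection.

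Under the literal per-protocol sentence that observed status is overwritten. The repeat of the primary analysis would then change the endpoint as well as the population. If the per-protocol effect came out weaker than the intention-to-treat effect, a reader could not tell whether the cause was treatment received, the other population rules or the scoring. A sound primary result might be described as failing a robustness check.

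**Working it through.** **Step 1: the two rules, patient by patient.**

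| Patient | Intention-to-treat | Per-protocol, literal reading | Per-protocol, narrow reading |
|---|---|---|---|
| Endpoint missing because of death or relaparotomy | infection | infection | infection |
| Relaparotomy, CDC infection observed | infection | infection | infection |
| Relaparotomy, observed infection-free to visit 6 | no infection | **infection** | no infection |

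The narrow reading takes the sentence as completing the second exclusion, so that it concerns only patients who miss visit 6 through death or relaparotomy. Only the third row separates the readings. Deaths before visit 6 usually leave the endpoint missing and are then scored alike.

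**Step 2: reproduce the plan's own figure.** Inputs from Sample size calculation: the infection rate "is approximately 25 % for the control group" and "can be reduced to 12.5 % in the experimental intervention arm". From these rates the protocol article derives its number per arm, 152, for a chi-square test with 80% power, and the test is "at a two-sided level of significance of 5"%. With pooled variance under the null and no continuity correction:

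n = [1.960·√(2·p̄·(1−p̄)) + 0.842·√(p₁(1−p₁) + p₂(1−p₂))]² / (p₁−p₂)²

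With p₁ = 0.25, p₂ = 0.125 and p̄ = 0.1875:

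n = (1.082 + 0.459)² / 0.125² ≈ 152 per group, power 80.0%.

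The stated figure reproduces and is not in dispute.

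**Step 3: size of the scoring difference under the literal reading.** Let r be the relaparotomy rate (assumed equal in both arms) and q the share of these patients observed infection-free. The protocol gives neither. A proportion x = r·q of each arm moves from no infection to infection:

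p₁′ = 0.25 + x, p₂′ = 0.125 + x, RR′ = p₂′/p₁′

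The last row of the table below instead assumes that relaparotomy is unrelated to infection and that every such patient is assessed. The rates then become p + (1−p)·r: 0.25 + 0.75·0.10 = 0.325 and 0.125 + 0.875·0.10 = 0.2125.

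| Assumption | Control | NPIT | RR | OR | Rescored per 152 | Power at 152 per group |
|---|---|---|---|---|---|---|
| q = 0, any r | 25.0% | 12.5% | 0.50 | 0.43 | 0 | 80% |
| r = 3%, q = 25% | 25.75% | 13.25% | 0.515 | 0.44 | 1.1 | 79% |
| r = 5%, q = 50% | 27.5% | 15.0% | 0.55 | 0.47 | 3.8 | 76% |
| r = 10%, q = 50% | 30.0% | 17.5% | 0.58 | 0.50 | 7.6 | 73% |
| r = 10%, unrelated to infection, all assessed | 32.5% | 21.25% | 0.65 | 0.56 | 11.4 control, 13.3 NPIT | 60% |

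In the rows with a common x the absolute difference stays at 12.5 percentage points and only the ratio measures shrink. In the last row it falls to 32.5 − 21.25 = 11.25 points. The planned model is logistic, so the odds ratio is the scale on which a reader would see the change. The power column shows scale only: 152 is the planned number analysed per group, not a per-protocol sample size. All rows hold the true infection rates and the treatment effect on them fixed.

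**The case against.** The strongest reply is that there may be no mismatch. The per-protocol sentence comes straight after an exclusion about patients who do not reach visit 6. Read together, the two say that patients lost for other reasons leave the population, while those lost through death or relaparotomy stay in and count as infected. That is the intention-to-treat rule. This reading is plausible and must be allowed. It does not dispose of the point: the sentence stands alone, has no limiting clause and omits the missing-data condition used in the section just before it. Two analysts could score the same patient differently.

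The affected group is also narrow and of unknown size, and relaparotomy is unlikely to be independent of infection when Table 1 names reoperation as a place where infection is found. That stands, and it makes the last row of the table an upper-end case. The plan's 80% power belongs to the primary analysis and none is claimed for the per-protocol analysis, so a fall to 60% is not a loss of planned power.

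The repeat in the surgical site infection population (patients who reached visit 6, as randomized, with no death or relaparotomy rule) offers a partial cross-check. With equal relaparotomy rates, the distortion is towards no effect. Both points limit the harm, but unequal rates could shift the result either way.

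A reader might infer that the scoring rule by itself prevents the per-protocol analysis from showing the effect of adherence. The documents do not support that. The population is grouped as treated, its listed exclusions set no minimum NPIT wear time, and it drops losses to follow-up that intention-to-treat counts as no infection. It would not isolate adherence even with the sentence corrected.

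**Conclusion.** The point holds as a wording conflict in a sensitivity analysis. Literally read, the per-protocol rule replaces an observed infection-free CDC status with an event, while the primary analysis keeps that status. A gap between the two results could then not be put down to treatment received alone. On the narrow reading the rules agree, and the text does not say which is meant.

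The effect runs from nothing (no relaparotomy patient observed infection-free) through a risk ratio of about 0.52 to 0.58 in moderate cases, to 0.65 in the upper-end case shown. Every non-zero figure rests on assumed relaparotomy rates, equal in both arms, because the protocol gives none. The primary endpoint, primary analysis and sample size are untouched.

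**What to change.** In Per-protocol population, replace the last sentence with the intention-to-treat rule: count a patient as infected on account of death or relaparotomy only where the CDC status is missing for that reason; otherwise analyse the observed CDC status.

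If a composite of infection, relaparotomy or death is wanted, define it under its own name and report it in both populations, so that the endpoint and the population do not change together.

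The cost is one sentence, with no new data and no change to the sample size. It should be settled before unblinding, so that scoring is not left to discretion.

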##### Surgical site infection population

The surgical site infection population contains all patients included in the intention-to-treat population who have reached the study end (visit 6), independent of the treatment they have received (‘as randomized’).

##### Safety population

The safety population contains all patients who have started visit 2 independent of the treatment they have received (analysis ‘as randomized’).

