#### Safety analysis

For safety analysis, all adverse and serious adverse events will be analyzed via descriptive statistical methods. For comparisons of frequencies between groups, the chi-square test and, if appropriate, the Fisher exact test, will be used. Patients who have started visit 2 (operation) will be analyzed as treated.

Procedures for the statistical analysis of the primary and secondary endpoint measures will be conducted in line with the GCP-ICH E9 guideline [40]. For the statistical analysis, IBM SPSS Statistics version 21.0 will be used (IBM Corp., Armonk, NY). Statistical analysis will be performed by a group-allocation blinded statistician from the Institute for Medical Statistics and Epidemiology of the Technische Universität München.

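### The safety population is to be analysed as randomized in one section and as treated in another, and nothing in the protocol reconciles the two rules

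*Protocol article*

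**What the plan says.** Two sections of the protocol article set the rule for assigning patients to arms in the safety analysis.

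- Safety population, under Analysis populations: "all patients who have started visit 2 independent of the treatment they have received (analysis ‘as randomized".
- Safety analysis, under Statistical methods: "Patients who have started visit 2 (operation) will be analyzed as treated".

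Both define the set by entry into visit 2, so the patients are the same. The Safety analysis section describes the work as descriptive ("all adverse and serious adverse events will be analyzed via descriptive statistical methods") but also plans tests between the arms: "For comparisons of frequencies between groups, the chi-square test and, if appropriate, the Fisher exact test, will be used".

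Two other definitions bear on the reading. The per-protocol definition sets the two terms against each other: "The per-protocol population contains all patients included in the intention-to-treat population as treated (not as randomized". The intention-to-treat definition allows for treatment that differs from allocation: "independent of the intervention they receive (control or NPIT). Analysis will occur as randomized". The Outcome measures section also lists a safety-type secondary endpoint: "Number of postoperative severe adverse events in both groups within 30 days".

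**The concern.** The two sections give incompatible instructions for one analysis. Take a patient allocated to standard dressing who is given the negative-pressure device. Under the population definition, all of that patient's adverse events count in the control arm. Under the analysis section they count in the device arm. An analyst can follow one section only by departing from the other.

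This is not a detail left to a fuller document. The rule is stated twice, and the statements conflict.

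The as-randomized rule has a predictable effect on a harm that the device really causes. Events in control-allocated patients who received the device raise the control rate, and device-allocated patients who never received it lower the device rate. Both move the comparison towards no difference. Leaving the choice open also allows it to be made after the results are known.

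**Working it through.** **Step 1: compare the texts.**

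| Section | Patients | Rule |
|---|---|---|
| Safety population | all who started visit 2 | as randomized |
| Safety analysis | all who started visit 2 | as treated |
| Per-protocol population | a subset of the intention-to-treat population | as treated, expressly not as randomized |

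The third row rules out reading the two terms as synonyms. No section says that one rule prevails or that both analyses will be run.

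**Step 2: when do the rules differ?** They differ only for patients whose dressing is not the one allocated. If there are none, every patient is in the same arm under both rules.

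**Step 3: illustrate the size.** The article states no figure on this point, so there is none to reproduce.

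Inputs:

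- 170 patients per group, from the Sample size calculation section.
- Event risk of 10% on the device and 2% on standard dressing. This is an assumption and is not in the article.
- A fraction c of an arm receives the other dressing. This is an assumption, shown at 0, 5% and 10%.
- Risk depends only on the dressing received. This is also an assumption.

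Formulas, with crossover c in each direction:

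- As treated: 10% − 2% = 8.0 points, whatever c is.
- As randomized, device arm: (1 − c) × 10% + c × 2%.
- As randomized, control arm: c × 10% + (1 − c) × 2%.
- As-randomized difference: (1 − 2c) × 8.0 points.
- Patients counted in different arms under the two rules: 2 × 170 × c.

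| c in each direction | Patients who change arm | Device, as randomized | Control, as randomized | Difference, as randomized | Difference, as treated |
|---|---|---|---|---|---|
| 0 | 0 | 10.0% | 2.0% | 8.0 | 8.0 |
| 5% | 17 | 9.5 + 0.1 = 9.6% | 0.5 + 1.9 = 2.4% | 7.2 | 8.0 |
| 10% | 34 | 9.0 + 0.2 = 9.2% | 1.0 + 1.8 = 2.8% | 6.4 | 8.0 |

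If only device-allocated patients cross over, the control rate stays at 2.0%. The as-randomized difference is then 9.6 − 2.0 = 7.6 points at 5% and 9.2 − 2.0 = 7.2 points at 10%.

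In all these scenarios the as-randomized rule attenuates the difference and does not reverse it.

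**The case against.** The strongest objection is that the conflict may have little practical effect. Randomization takes place in theatre after the skin is closed, and the device goes on immediately afterwards, so there is little time for a patient to receive the wrong dressing. Early removal of the device is not crossover, because the patient has still received it. The safety analysis is also narrower than all device harm. Surgical site infection and expected postoperative events up to Dindo–Clavien grade I are not recorded as adverse events, and blistering is captured separately as another wound complication. All of this stands. It limits the size of the problem but does not settle which rule applies.

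A second objection is that an as-treated comparison gives up the protection of randomization if the patients who switch are unusual. That is fair, and it is a reason why some readers may want the as-randomized table as well. It does not justify stating both rules as the rule for one analysis.

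Two stronger readings are tempting.

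- **The choice of rule could reverse a safety comparison.** With nearly equal, very small counts this can be constructed: 2 device events against 3 control events becomes 3 against 2 if one of the control events was in a patient who received the device. The article gives no crossover rate or adverse-event rate that makes such a case likely, and the scenarios above show attenuation only.
- **The comparison of serious adverse events is a secondary endpoint and so depends on the rule.** The listed endpoint concerns severe events, and the safety reporting section uses severe as an intensity grade within serious events. The section on secondary endpoints names no analysis population. The endpoint may be affected, but the article does not establish it.

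**Conclusion.** The contradiction holds on the text alone: the same patients and the same analysis have two opposite rules, with no reconciliation. Its consequence is confined to safety reporting. The as-randomized rule would dilute a true device harm in the planned chi-square or Fisher comparisons. In the illustration the loss is 0.8 points at 5% crossover in each direction and 1.6 points at 10%, from a difference of 8.0. It is zero without crossover. These sizes rest entirely on the assumed event risks and crossover rates. The article gives neither, and its design suggests that crossover could be low.

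The primary intention-to-treat analysis, its significance level and its sample size are not touched. This is a modest defect that should be corrected because it is certain and cheap to remove.

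**What to change.** Before unblinding, replace the as-randomized rule in the Safety population section with as treated, meaning by the dressing actually received, so that it matches the Safety analysis section. Membership of the population, defined by having started visit 2, need not change. An additional as-randomized table is optional.

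The cost is one phrase in the protocol, carried into the statistical analysis plan. It needs no new data beyond a record of the dressing received, which the per-protocol analysis already requires.

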#### Analysis of the primary endpoint measure

The analysis of the primary endpoint measure will be performed in the intention-to-treat population. The statistical hypothesis is:$$ {H}_0:{\varPi}_{\mathrm{T}}={\varPi}_{\mathrm{C}}\kern1em \mathrm{versus}\kern1em {H}_{\mathrm{A}}:{\varPi}_{\mathrm{T}}\ne {\varPi}_{\mathrm{C}} $$where Π_T_ is the rate of surgical site infections in the NPIT group and Π_C_ the rate of surgical site infections in the control group. Rates of surgical site infection will be analyzed via multivariate binary logistic regression with centre effects and possible baseline differences between intervention and control group. The level of significance will be set at 5 %.

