#### Prespecified subgroup analysis

Prespecified subgroup analysis will be performed in the surgical site infection population for the depth of surgical site infection (superficial versus deep versus organ space; Table 1) in both groups (NPIT versus control). Furthermore, the rate of all surgical site infections will be analyzed in the surgical site infection population in the following subgroups: (a) National Nosocomial Infection Surveillance risk score (0 versus 1 versus >1); (b) body mass index (<25 versus >25); (c) grade of contamination (clean versus clean-contaminated versus contaminated versus dirty, as defined by the CDC, [9]); (d) American Society of Anesthesiology score (1 and 2 versus 3 versus ≥4); (e) presence of an ostomy (yes versus no); (f) skin preparation used (ethanol-based versus isopropyl-alcohol-based versus chlorhexidine-based versus Povidone-iodine-based); (g) age (≤65 versus > 65 years), (g) cause of surgery (malignant versus benign surgery).

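### The primary logistic model takes its covariates from apparent baseline differences between the arms, with no criterion, instead of from a fixed prognostic list

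*Protocol article*

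**What the plan says.** Under Analysis of the primary endpoint measure, the null hypothesis is equal infection rates in the two groups. The test is a "multivariate binary logistic regression with centre effects and possible baseline differences between intervention and control group" at the 5% level. Nothing else in the document describes this model. The section gives no covariate names, no threshold for a difference, and no statement that the set is fixed beforehand or deferred to another document.

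Three other places bear on the point:

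- **Sample size calculation.** The infection rate "is approximately 25 % for the control group" and "can be reduced to 12.5 % in the experimental intervention arm". On that basis "a group sample size of 152 patients would need to be compared using the chi-square test". The stated aim is 80% power, two-sided at 5%. With drop-out, "a total of 340 patients (170 per group) need to be enrolled in the study".
- **Prespecified subgroup analysis.** Eight patient or operative factors are listed: the NNIS risk score, body mass index, contamination grade, ASA score, ostomy, skin preparation, age and cause of surgery. They serve as subgroups only.
- **Randomization and blinding; Safety analysis.** Centre is the only stratification factor. Allocation takes place after skin closure. The statistician is blinded to group.

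**The concern.** The section states a principle for choosing covariates, and the principle is the wrong one. After proper randomisation, a baseline difference between arms is a chance event. A variable is worth adjusting for because it predicts infection. Choosing by imbalance can admit variables unrelated to infection and leave out predictive ones that happen to be balanced.

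The second difficulty is that a difference is not defined. It could mean a significance test at one of several cut-offs, a standardised difference, or judgement. Each reading can give a different model and so a different primary p-value, and the choice would be made with baseline data, and possibly outcomes, in view. What is at stake is how firmly the primary test is fixed, and a modest gain in power from data that the trial needs anyway.

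**Working it through.** **1. The plan's own figure.** Inputs from Sample size calculation: rates 0.25 and 0.125, two-sided alpha 0.05, power 0.80. The mean rate is 0.1875. Chi-square formula with pooled variance and no continuity correction:

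n = [1.960·√(2·0.1875·0.8125) + 0.842·√(0.25·0.75 + 0.125·0.875)]² / 0.125²
= [1.960·0.5520 + 0.842·0.5449]² / 0.015625 ≈ 151.9, so 152 per group.

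Power at 152 per group is 80.0%. The plan's figure reproduces, and it takes no credit for covariate adjustment.

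**2. How often the undefined criterion matters.** Take the eight subgroup variables as candidates and treat them as independent (an assumption). The chance that at least one differs between arms is 1 − (1 − c)^8 for cut-off c:

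- p<0.05: 1 − 0.95^8 = 34%
- p<0.10: 1 − 0.90^8 = 57%
- p<0.20: 1 − 0.80^8 = 83%

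The unstated cut-off would often decide which model is primary.

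**3. Type I error and power by simulation.** Assumptions: 152 per arm; eight independent standard normal covariates, three of them prognostic with log-odds 0.4 or 0.6 per SD; 25% in both arms under the null and 25% v 12.5% under the alternative; Wald test; centre left out; 3000 trials per scenario. Monte Carlo standard error is about 0.4 points for type I error and 0.7 for power.

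| Analysis | Type I %, 0.4 | Type I %, 0.6 | Power %, 0.4 | Power %, 0.6 |
|---|---|---|---|---|
| Unadjusted | 4.8 | 4.4 | 79.6 | 79.4 |
| Imbalance at p<0.05 | 4.7 | 4.1 | 79.4 | 79.9 |
| Imbalance at p<0.10 | 4.5 | 4.1 | 79.7 | 80.6 |
| Imbalance at p<0.20 | 4.3 | 3.8 | 80.0 | 81.6 |
| Standardised difference >0.1 | 4.3 | 4.0 | 80.2 | 82.4 |
| Smallest p of the five rows above | 6.2 | 6.0 | – | – |
| Smallest p, no covariate or any one of eight | 7.0 | 7.2 | – | – |
| Fixed three prognostic covariates | 5.0 | 4.7 | 81.9 | 85.4 |

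Gain of the fixed set over the imbalance rules: at 0.4, from 81.9 − 80.2 = 1.7 to 81.9 − 79.4 = 2.5 points; at 0.6, from 85.4 − 82.4 = 3.0 to 85.4 − 79.9 = 5.5 points.

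**4. Other settings.**

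- With 340 patients, five of eight covariates prognostic at 0.3–0.6 per SD, and 6000 runs, type I error was 4.5% for the p<0.10 rule and 6.7% for the best of five cut-offs. Power was 84.8% for the p<0.10 rule and 88.9% for the fixed set, a gain of 4.1 points.
- A further simulation at 152 per arm with eight candidates gave 4.4–5.1% for single cut-offs, about 5.5–6.7% for the smallest p across cut-offs, and a gain of about 1–5 points.

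**5. Room in the model.** Expected events at the planned rates: 170·0.25 + 170·0.125 = 63.75, about 64. Fifteen centres use 14 parameters, so few covariates can be added safely.

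**The case against.** **Covariate lists usually belong in a statistical analysis plan.** This stands as far as the missing list goes: its absence is no fault in an article. It does not rescue the wording, because the section states a selection principle and does not defer the choice.

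**The sentence does not strictly prescribe selection by imbalance.** It could mean factors in which the groups might differ. Imbalance is the more natural reading, but the text is ambiguous, and the point should be put that way.

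**A reader might infer that the 5% level holds only if the model is fixed.** The figures do not support this: each single imbalance rule was at or slightly below 5%. The excess appears only if several analyses are run and the smallest p-value is used. Blinding the statistician lowers that risk, but only in part, since baseline differences and two-sided p-values can be seen with coded arms.

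**A reader might infer that promised power is lost, or precision given up.** Neither follows. The 80% rests on an unadjusted test and reproduces. In logistic regression, prognostic adjustment raises the standard error of the log odds ratio (median 0.293 unadjusted and 0.324 adjusted in a 3000-run check with 340 patients). Power rises because the estimate moves further from zero.

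**A reader might infer that an adjusted odds ratio tests the wrong hypothesis.** It does not. With no treatment effect, an odds ratio of 1 and equal rates coincide.

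**The remedy also has a price.** A combined run with 15 uneven centres and five covariates gave type I error of 5.2%, 6.0% and 5.8% at common rates of 25%, 18.75% and 12.5% (standard error about 0.4 points). This is acceptable, but it argues for a short list.

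**Conclusion.** The concern holds as a fault in the stated principle, and its size is moderate. The wording ties adjustment to chance differences, gives no criterion, and so leaves the primary model open until the data are seen.

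- **Type I error:** about 4–5% under any one rule applied mechanically; about 6–7% if the analyst chooses among defensible readings, with partial protection from blinding.
- **Power:** the planned 80% stands. A fixed prognostic set would add roughly 1 to 5 points over the imbalance rule.

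The power gain assumes three to five covariates with log-odds of 0.3–0.6 per SD. It also assumes that the chosen covariates are the predictive ones, so weaker or badly chosen covariates would gain less. Centre adjustment is sound: it matches the stratification, and a separate simulation with 15 unequal centres as fixed effects gave type I error of 4.8–5.0%. The change is worth making because it governs the primary p-value and costs almost nothing.

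**What to change.** Under Analysis of the primary endpoint measure, replace the clause on baseline differences with a short list of prognostic covariates, fixed before any outcome data are seen and always included whatever the observed balance, together with centre. Choose them from the variables already required for the subgroup analyses, for example NNIS risk score, body mass index, ostomy and age. Because allocation follows skin closure, operative factors such as ostomy precede it and are valid covariates. Keep the list short, given about 64 expected events and 14 centre parameters.

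The cost is a sentence or two and a few more model parameters, with no new data. Trial status still describes recruitment as planned, so the change can precede all outcomes. Reporting a standardised risk difference with its confidence interval beside the odds ratio would suit an objective stated in rates, but it is an optional extra and corrects no error.
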